^. Candidate vaccines which have passed successfully through phase I trials and are in Phase 2b efficacy studies could be included in a TB CHIM, which could be designed to either measure prevention of infection (POI) or immunological endpoints. This would allow vaccine discovery to accelerate in a cost-effective manner. Similarly, a responsive TB CHIM could accelerate the development of new drugs and promote refinement of drug combination regimens.

There are current concerns in using wild type
*M.tb* as a human challenge agent given that infection cannot be reliably eradicated, treatment is prolonged with toxicities and there is a risk of relapse or recurrent infection
^
11
^. BCG contains live attenuated
*Mycobacterium bovis* which forms part of the
*Mycobacterium tuberculosis* complex and is replication competent but does not usually cause clinical TB disease in immunocompetent individuals. A recent systematic review and workshop discussion of TB CHIM in the UK and Malawi identified several CHIMs using BCG
^
11
^. Intradermal injection with BCG was associated with expected side effects following routine vaccination with no serious adverse events (SAEs) reported in any of the identified studies. Disseminated BCG-disease has been reported in infants after routine intradermal vaccination and after intravesical installation (as chemotherapy to prevent recurrences of carcinoma in situ and/or Ta/T1 papillary tumours of the bladder) but this is extremely uncommon, primarily affecting immunocompromised individuals and readily treatable using standard anti-tuberculosis therapy
^
12
^. The workshop discussion agreed that BCG was currently the preferred agent to optimise a TB CHIM as it is licensed worldwide, has a long-established safety profile, is usually selected as the control agent in novel vaccine studies, and has been reliably recovered from previous challenge models with optimised dosing.

We are working in collaboration with partners at the University of Oxford who have established a CHIM using intradermal BCG and have published several peer reviewed articles
^
13–
16
^. They found optimal BCG recovery with punch biopsies at 2 weeks post intradermal BCG injection and using three times the standard BCG dose, without additional adverse events
^
15

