## Protocol

### Objectives and outcome measures

**
Overarching aim
**

To establish the safety and feasibility of an established BCG controlled human infection model in Liverpool, UK.

**
Specific objectives (
Table 1)
**

1.   Confirm microbiological and molecular recovery of BCG at the intradermal injection site by gold standard skin punch biopsy (punch biopsy) 14 days after challenge

2.   Confirm safety and tolerability in healthy adult participants

3.   Determine agreement between less invasive skin biopsy techniques (including swabs, skin scrapes and microbiopsy) compared to gold standard punch biopsy on microbiological and molecular recovery of BCG with an aim to employ less invasive methods within a refined protocol in future.

4.   Confirm optimal procedures to assess immune response to BCG intradermal challenge locally (skin tissue), systemically (blood) and in the respiratory mucosa (nasal samples).

**Table 1. T1:** Outcome measures: Objectives and endpoints.

	Objectives	Endpoints
**Primary**	To quantify BCG recovered from the intradermal BCG challenge site 14 days after injection	Culture and PCR quantification of BCG at intradermal challenge site by punch biopsy
**Secondary**	Confirm safety and tolerability of study procedures in participants	Actively (solicited) and passively collected data on adverse events
	Confirm agreement between BCG recovery between punch biopsy and minimally invasive skin biopsy	Pairwise comparison between culture and PCR quantification by punch and micro skin biopsy
	Confirm agreement between BCG recovery between punch biopsy and minimally invasive skin scrape	Pairwise comparison between culture and PCR quantification by punch biopsy and skin scrape
	Longitudinal quantification of BCG recovery from the intradermal BCG challenge site at 2, 7, 14, 21 and 28 days	Culture and PCR quantification of BCG at intradermal challenge site by non-invasive skin swab.
	Confirm laboratory assays for immune response to BCG at intradermal injection site	Skin biopsy cell pellet(s) examined for immune cell differentiation and antigen stimulation
	Confirm laboratory assays for immune response to BCG in systemic circulation	Immune cell activation and functional assays; and cytokine levels in blood
	Measure immune response to BCG injection in respiratory mucosa	Nasal scrape pellet and nasal lining fluid examined for cell differentiation and activation and cytokine expression

**
Study hypotheses
**

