### Study design

Prospective longitudinal controlled human infection study after intradermal injection with BCG SSI in two phases: Phase A is designed to confirm microbiological recovery and determine agreement between the current gold standard of skin punch biopsy 14 days after injection with minimally invasive biopsy techniques. Phase B is designed to refine and optimise immunological assays to measure local (using optimal minimally invasive techniques), systemic (blood) and respiratory mucosal responses to intradermal BCG injection.

**
Phase A
**

Ten participants will receive a single intradermal injection to the upper arm of BCG SSI 6–24 × 10
^5^ colony forming units in line with an optimised and established existing protocol
^
15
^. The BCG SSI strain has been chosen as the UK licensed vaccine for TB. The dose (3x higher than that used in routine vaccination) has been chosen based on study findings by Minhinnick
*et al.*
^
15
^, who demonstrated good mycobacterial recovery at this concentration with no increase in participant adverse events between the doses. Participants will be followed up longitudinally with active assessment for tolerability; adverse events; and serious adverse events. We will determine BCG SSI recovery from the intradermal injection site 14 days later by classical microbiology and molecular diagnostic techniques using gold standard punch biopsy
^
15
^ as our primary outcome measure. In parallel, and after local anaesthetic injection, we will obtain paired minimally invasive samples (skin swab, skin scrape
^
18
^ and microbiopsy
^
17
^ from the same skin site at 14 days and determine agreement of BCG SSI recovery by classical microbiology and molecular diagnostic techniques with punch biopsy

Parameters for progression from Phase A to Phase B are:

1.Participants able to tolerate study procedures2.No experimental challenge related SAE or SUSAR detected3.Confirmation of BCG recovery by classical microbiology or molecular techniques from punch biopsy at day 14 in all 10 participants who received intradermal BCG challenge4.Confirmation of BCG recovery by classical microbiology or molecular techniques from any of the minimally invasive skin sample technique (swab, scrape and microbiopsy) at day 14 in ≥9 participants who received intradermal BCG challenge.

**
Phase B
**

Twenty participants will receive a single intradermal injection to the upper arm of BCG SSI 6–24 × 10

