**Preparation and administration of mycobacteria**
*

*Formulation and supply*

BCG SSI contains live attenuated Danish strain 1331
*Mycobacterium bovis* BCG. It is supplied as a powder and solvent for suspension. One vial of SSI reconstituted in 1mL contains 10 doses of 2–8 × 10
^5^ CFU (see SmPC). BCG SSI will be supplied to the Accelerator Research Clinic by the Liverpool University Hospitals NHS Foundation Trust who stock the vaccine for clinical use. All movements of the study challenge agents will be documented. Challenge agent accountability, storage, shipment and handling will be in accordance with local SOPs. Drug movement will occur in a refrigerated container to ensure a cold chain of +2 to +8°C.

*Storage*

Dispensed BCG SSI vials are supplied in boxes containing multiple vials and each vial is clearly labelled with the market product (BCG SSI). All challenge agents to be administered will be stored in a safe and locked place with no access by unauthorised personnel. The BCG will be stored between +2
^o^C and +8°C in a locked fridge. The storage conditions will be under the responsibility of the clinical site. Any temperature deviation outside the range +2 to 8°C will be reported to the CI as soon as detected. Following an exposure to such a temperature deviation, challenge agents will not be used until CI approval has been given.

*Administration*

The correct volume will be drawn up and administered intradermally over the deltoid region of the non-dominant upper arm, according to the site-specific SOP. One vial of SSI reconstituted in 1mL contains 10 doses of 2 – 8 × 10
^5^ CFU (*taken as 5×10
^5^ CFU for this calculation). To achieve the specified dose of 6 – 24 × 10
^5^ CFU we plan to reconstitute in 0.4ml (3 doses 0.1ml doses for administration and an additional dose for post hoc checking of dose administered) This volume will be checked in the laboratory prior to study commencement and may be subject to change in order to achieve the target concentration. We will review the administration concentrations after phase A and may adjust reconstitution volumes to refine the BCG dose in Phase B. Intradermal injection will be standardised in the study by using the FDA marked 0.6mm MicronJet microneedle (

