https://www.nanopass.com/). After intradermal injection, participants will stay in the unit for 15 minutes and have a clinical review at this point. During the administration of the challenge agent, resuscitation medicines and equipment will be immediately available for the management of anaphylaxis.

**
Safety procedures
**

Written and verbal instructions are given to the participant describing potential mild, moderate and severe symptoms and the instances to consult the study team.

Participants will be instructed to monitor the development of any symptoms and report them to the clinical team immediately. Home monitoring of symptoms will include a clear flow chart of the necessary intervention should any symptoms develop (see participant safety information sheet).

**
Confirmation and quantification of mycobacterial recovery
**

Skin biopsy specimens will be cryopreserved and subsequently processed in batch. Typically, each biopsy specimen will be thawed in a 37°C water bath and transferred to an appropriate tissue homogenising platform
^
16
^. A total of 100 μL of neat homogenate and 100 μL of a 10
^-1^ dilution, in sterile PBS, will be plated in triplicate onto Middlebrook 7H11 agar. The BCG SSI vaccine vials will be reconstituted in PBS, and 100 μL of appropriate dilutions will be plated in triplicate as positive controls. Plates will incubated at 37°C for 4 weeks before counting. The remaining biopsy specimen homogenate will be stored at −80° for subsequent DNA extraction.

**
DNA extraction
**

Biopsy specimen homogenate will be thawed, and BCG DNA from 200 μL of homogenate will be released using standard methods. Typically, a tough microorganism (bead beating) lysing kit will be used. Homogenate will be transferred to a separate tube and 50 μL PBS used to wash remaining homogenate from the beads. A total of 180 μL of ATL buffer and 20 μL of proteinase K (Qiagen) will be added, and the homogenate vortexed and incubated at 56°C for 4 hours. Following this step, extractions will be performed as previously described
^
16
^.

**
Quantitative polymerase chain reaction
**

Appropriate primers be used for detection of BCG DNA. These are optimised modifications
^
16
^ of an early template complementary to regions flanking the BCG deletion sequence, RD1, and amplify a 196–base pair fragment
^
22
^. Polymerase chain reaction (PCR) analyses will be performed as previously described
^
16

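### The dose each participant receives may vary fourfold and will be measured, but the measurement has no stated role in the between-participant recovery analyses or the immune correlations

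*Protocol article*

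**What the plan says.** **Dose.** Study design, Phase A, states: "Ten participants will receive a single intradermal injection to the upper arm of BCG SSI 6–24 × 10"^5 CFU. Phase B repeats the range and adds that it will be informed by the concentrations given in Phase A. The reason for the choice is recovery: "The dose (3x higher than that used in routine vaccination) has been chosen based on study findings". The Introduction says of the collaborating group: "They found optimal BCG recovery with punch biopsies at 2 weeks post intradermal BCG injection and using three times the standard BCG dose".

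**Preparation.** In Preparation and administration of mycobacteria, the vial content is given as "One vial of SSI reconstituted in 1mL contains 10 doses of 2–8 × 10"^5 CFU, with 5 × 10^5 as the working value. The plan is to reconstitute in 0.4 ml, giving "3 doses 0.1ml doses for administration and an additional dose for post hoc checking of dose administered". The same paragraph provides for a laboratory check of the volume before the study. It also provides for a review of administered concentrations after Phase A, which may change the volumes used in Phase B.

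**Endpoint and analysis.** The primary endpoint in Table 1 is "Culture and PCR quantification of BCG at intradermal challenge site by punch biopsy". Statistical methods names Pearson's correlation between the primary endpoint and the secondary immunological outcomes. Neither place has a dose term.

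**Progression.** Criterion 3 requires confirmed recovery by culture or molecular methods "from punch biopsy at day 14 in all 10 participants who received intradermal BCG challenge". Criterion 4 requires it by any minimally invasive technique in at least nine.

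**The concern.** The protocol chose its dose because recovery depends on dose, so recovery is partly a read-out of what was injected. Two participants can differ up to fourfold in inoculum and both be within specification. Part of the difference in their day-14 counts then reflects the vial and not the host. Everyone dosed from one vial shares its inoculum, so this part is a batch effect. Because volumes may change between phases, a difference between Phase A and Phase B may also be partly a dose difference.

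Two uses of the data are exposed. The study is meant to provide pilot data for later interventional trials, and those trials would take their between-participant SD of recovery from here. The correlation with immune outcomes would also be diluted if dose drives only recovery, or partly manufactured if dose drives both.

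The retained aliquot is the means of separating these effects. Its only stated use is to inform volumes for Phase B.

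**Working it through.** **Inputs from the protocol.** Dose 6–24 × 10^5 CFU; vial of 10 doses of 2–8 × 10^5 CFU (nominal 5); reconstitution in 0.4 ml; three 0.1 ml doses administered per vial plus one retained; n = 10 and n = 20; one injection per participant.

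**Inputs assumed, because the protocol gives none.** SD of log10 recovery from all sources other than dose, 0.2 to 1.0; delivered dose log-uniform over the permitted range; recovery proportional to dose; all dose variation lying between vials.

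**1. The protocol's own dose figure.** Dose per 0.1 ml = 10 × CFU per dose × 0.1/0.4 = 2.5 × CFU per dose.
- Low: 2.5 × 2 = 5. Nominal: 2.5 × 5 = 12.5. High: 2.5 × 8 = 20 (all × 10^5 CFU).
- The planned volume therefore gives 5–20 × 10^5 CFU, or 2.5 times the routine dose. The stated figures are 6–24 × 10^5 and three times. They are not reproduced, and the low end falls below the specified minimum.
- The span is fourfold either way (24/6 = 20/5 = 4), so the steps below do not depend on which statement is corrected.

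**2. Vials.** At three participants per vial, Phase A needs at least ceil(10/3) = 4 vials and Phase B at least ceil(20/3) = 7. That is as few as 11 inocula for 30 people if every vial is fully used.

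**3. Dose share of between-participant variance.** SD of log10 dose = log10(4)/√12 = 0.602/3.464 = 0.174; variance 0.0302. Share = 0.0302/(0.0302 + SD²).

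| Assumed other SD (log10) | Other variance | Dose share |
|---|---|---|
| 0.2 | 0.04 | 43% |
| 0.3 | 0.09 | 25% |
| 0.5 | 0.25 | 11% |
| 0.7 | 0.49 | 6% |
| 1.0 | 1.00 | 3% |

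**4. Consequence for a later trial.** Sample size for a mean difference is proportional to variance. Leaving dose in multiplies it by 1 + 0.0302/SD²: 1.34, 1.12 and 1.06 for SD 0.3, 0.5 and 0.7.

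**5. Consequence for the correlation (on the log10 scale).** If dose affects recovery but not the immune read-out, the correlation is multiplied by √(1 − share): 0.87, 0.94 and 0.97 for the same SDs. If dose affects both equally and the other SDs are equal, dose alone creates a correlation equal to the share: 0.25, 0.11 and 0.06.

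**6. Where dose cancels.** For one injection, log10(punch/d) − log10(microbiopsy/d) = log10 punch − log10 microbiopsy, where d is the delivered dose. The same holds for log10 changes over time within one person. Dividing by d changes none of these.

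**7. Progression criteria.** Criterion 3 passes with probability p^10 if p is the common probability of detection: 0.99^10 = 0.90 and 0.90^10 = 0.35. It is sensitive to detection, but the protocol gives no figure linking dose to detection, so no dose effect on it can be computed.

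**The case against.** The strongest case against is that this is an analysis-plan detail in a feasibility study not sized for significance. The analysis plan is not shown, nothing in the protocol forbids dose adjustment, and the measured dose would be available to it. The plating method for the retained aliquot may sit in a site procedure. The only vaccine plating described, "The BCG SSI vaccine vials will be reconstituted in PBS, and 100 μL of appropriate dilutions will be plated in triplicate as positive controls", is not stated to be that aliquot, but an article may condense this. The magnitude also rests on assumptions. The protocol supports three times the routine dose over other doses, not proportionality within the range. BCG replicates, which could weaken the link between inoculum and day-14 count. Actual vials may vary less than the permitted span.

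Most of this stands as a limit on size. It does not remove the point, because this document itself defines the primary quantity, names the correlation and gives the measured dose a single use.

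Three stronger readings are tempting and unsupported:
- *Dose is checked only after the event.* The same paragraph provides for a volume check before the study and a concentration review after Phase A. What is measured only afterwards is the dose each participant actually received.
- *The progression criteria rest on raw quantities.* They are yes/no, by culture or molecular methods. A low vial matters only if it pushes recovery below detection by both. It would also be visible at the concentration review, so it need not be taken for failure of the model.
- *All recovery comparisons are distorted.* The punch versus minimally invasive comparisons and within-person changes are paired on one injection, and dose cancels.

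**Conclusion.** The point holds in a limited form. Between-participant day-14 recovery, any comparison or pooling across phases, and the correlation of recovery with immune outcomes carry vial-level dose variation that the trial plans to measure but assigns no analytic use beyond the volume review.

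On the assumptions above, dose accounts for about 25%, 11% or 6% of between-participant log10 variance at an other SD of 0.3, 0.5 or 0.7, and 3% to 43% over SDs of 1.0 to 0.2. The upper figures need a small residual SD. If vials vary less than the full span, or recovery rises less than proportionally with dose, the share is smaller. This does not threaten the feasibility conclusion, but it is worth correcting because the information is already being collected.

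The mismatch between the 0.4 ml volume and the stated dose is independent of these assumptions. The volume may change after the laboratory check, but as written the dose statements in Study design and in Preparation and administration of mycobacteria do not agree and must be reconciled. Which of them should change is not a matter for this review.

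**What to change.** 1. Record the vial identifier and the CFU measured in its retained aliquot against each participant.
2. Report between-participant recovery twice: raw, and relative to measured inoculum (log10 recovered minus log10 delivered), or with log10 measured dose as a covariate. The covariate form does not assume proportionality. Do the same for any comparison or pooling of Phases A and B.
3. Beside the planned Pearson correlation, give a partial correlation adjusted for log10 measured dose.
4. List each participant's measured inoculum next to the results for criteria 3 and 4. Leave the criteria themselves unchanged.
5. Reconcile the reconstitution volume, vial content, dose range and stated multiple of the routine dose.

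The cost is two data fields and a few extra columns, since the aliquot is already planned. The drawback is assay noise: an imprecise inoculum measurement adds error to the adjusted values and removes only part of the dose variance. The raw results should therefore be kept alongside.

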### Safety reporting

**
Definition of serious adverse events
**

Our safety reporting terms and definitions are described in
Table 4

**Table 4. T4:** Safety definitions. NB: to avoid confusion or misunderstanding of the difference between the terms “serious” and “severe”, the following note of clarification is provided: “Severe” is often used to describe intensity of a specific event, which may be of relatively minor medical significance. “Seriousness” is the regulatory definition supplied above.

Term	Definition
**Adverse Event (AE)**	Any untoward medical occurrence in a participant to whom a medicinal product or challenge agent has been administered, including occurrences, which are not necessarily caused by or related to that product.
**Adverse Reaction (AR)**	An untoward and unintended response in a participant to an investigational medicinal product or challenge agent which is related to any dose administered to that participant. The phrase "response to an investigational medicinal product or challenge agent" means that a causal relationship between a trial medication/challenge agent and an AE is at least a reasonable possibility, i.e. the relationship cannot be ruled out. All cases judged by either the reporting medically qualified professional or the Sponsor as having a reasonable suspected causal relationship to the trial medication/challenge agent qualify as adverse reactions. It is important to note that this is entirely separate to the known side effects for the challenge agent. It is specifically a temporal relationship between administration of challenge agent, the half-life, and the time of the event or any valid alternative aetiology that would explain the event.
**Adverse Event of** **Special Interest ** **(AESI)**	An adverse event of special interest (serious or non-serious) is one of scientific and medical concern specific to the challenge agent, for which ongoing monitoring and rapid communication by the investigator to the Sponsor can be appropriate. Such an event might warrant further investigation in order to characterise and understand it. Depending on the nature of the event, rapid communication by the trial Sponsor to other parties (e.g., regulators, DSMC) might also be warranted.
**Serious Adverse** **Event (SAE)**	A serious adverse event is any untoward medical occurrence that: • Results in death • Is life-threatening • Requires inpatient hospitalisation or prolongation of existing hospitalisation • Results in persistent or significant disability/incapacity • Consists of a congenital anomaly or birth defect Other ‘important medical events’ may also be considered serious if they jeopardise the participant or require an intervention to prevent one of the above consequences. NOTE: The term "life-threatening" in the definition of "serious" refers to an event in which the participant was at risk of death at the time of the event; it does not refer to an event which hypothetically might have caused death if it were more severe.
**Serious Adverse** **Reaction (SAR)**	An adverse event that is both serious and, in the opinion of the reporting Investigator, believed with reasonable probability to be due to one of the trial treatments/challenge agents, based on the information provided.
**Suspected** **Unexpected** **Serious Adverse** **Reactions (SUSAR)**	A serious adverse reaction, the nature and severity of which is not consistent with the information about the challenge agent.

**
Adverse events
**

Table 5 details the expected adverse events of BCG injection and challenge site biopsy

**
Adverse event severity assessment
**

Unexpected adverse events will be recorded and these AEs will be graded by severity as follows (where 0 = absent, 1 = mild, 2 = moderate, 3 = severe).
Table 6 details this process:

**
Causality assessment
**

The relationship of each adverse event to inoculation must be determined by a medically qualified individual within the study team according to the following definitions:

0 = No relationship:

•   No temporal relationship to BCG intradermal injection

•   Definite alternative aetiology (clinical, environmental or other intervention), and

•   Does not follow pattern of recognised response to BCG intradermal injection;.

1 = Unlikely relationship:

•   Unlikely temporal relationship to BCG intradermal injection or;

•   Alternate aetiology likely (clinical, environmental or other intervention), and

•   Does not follow pattern of recognised response to BCG intradermal injection

2= Likely relationship:

•   Reasonable temporal relationship to BCG intradermal injection, and

•   Event not readily explained by alternative aetiology (clinical, environmental or other interventions), and

•   Similar pattern of response to that seen to BCG intradermal injection, or

3 = Definite

•   Reasonable temporal relationship to BCG intradermal injection and

•   Event not readily produced by alternative aetiology (clinical, environment, or other interventions), and

•   Known pattern of response to BCG intradermal injection.

The chief investigator (CI), with the consultation of the trial steering committee (TSC), if required, will determine causality of AEs. The greatest degree of causal relationship (definite > probable > possible > unlikely related > not related) determined by either the PI or TSC after their discussions will determine the ultimate classification of the AE. Definite (4), probable (3) and possible (2) are considered to be related. No relationship (0) and unlikely (1) are unrelated.

**Table 5. T5:** Expected adverse events.

Expected adverse events
Pain/tenderness at the injection or biopsy site
Redness at the injection or biopsy site
Swelling at the injection or biopsy site
Warmth at the injection or biopsy site
Scaling/pustules at the injection or biopsy site
Transient ipsilateral axillary lymphadenopathy <1cm diameter
Scar at challenge (and biopsy site)
Headache
Fever (>38.3°C)

**
Procedure for recording adverse events
**

Participants will be asked to complete diary cards for 14 days after BCG challenge. They will be provided with a thermometer and tape measure to enable daily recording of temperature and local reactions at the injection site.

The diary cards will be reviewed at follow up visits and adverse events recorded in the CRF. Outside the diary card periods, expected local and systemic AEs (listed in
Table 5) will be specifically asked about and graded by severity (as detailed in
Table 6). Participants will be given the opportunity to report any other new symptoms since the last visit with start and stop dates and any treatments undergone.

All AEs (whether reported by the volunteer or solicited by the Investigator) will be clinically assessed at each visit and recorded in the CRF.

The following information will be recorded: description, date of onset and end date, severity and any treatment or intervention undertaken. The severity of events will be assessed on the following scale: 1 = mild, 2 = moderate, 3 = severe.

An assessment of relatedness to the BCG challenge will then be made by the Investigator.

AEs considered related to the BCG challenge as judged by a medically qualified investigator or the Sponsor will be followed either until resolution, or the event is considered stable.

**Table 6. T6:** Grading of adverse events.

Adverse Event	Grade	Measurement
Pain/tenderness at the injection or biopsy site	0 1 2 3	No pain at all Painful on touch, easily tolerated Painful when limb is moved, interferes with daily activity Severe pain at rest, interferes with daily activity
Redness at the injection or biopsy site	0 1 2 3	0mm 1–50mm 51–100mm >100mm
Swelling at the injection or biopsy site	0 1 2 3	0mm 1–20mm 21–50mm >50mm
Fever (oral)	0 1 2 3	≤37.5°C 37.6 – 38.0°C 38.1 – 38.9°C ≥39.0°C
Other AEs	0 1 2 3	Absence of symptom Awareness of symptom but tolerated; transient or mild discomfort; little or no medical intervention required Mild to moderate discomfort leading to interference with usual activity, some minimal medical intervention/therapy may be required. Significant interference with daily activity; some assistance usually required; medical intervention/therapy required; hospitalisation possible

**
Reporting procedures for Serious Adverse Events (SAEs) and Suspected Unexpected Serious Adverse Reactions (SUSARs)
**

Any serious adverse event considered by the CI to be related to the challenge agent and unexpected will be reported to the REC. As the challenge agents are vaccines with Marketing Authorisation, the mechanism for reporting any SAEs to the MHRA is via yellow card.

**
Follow up and outcome of adverse events
**

Those adverse events which are unexpected and likely to be related to the BCG, whether serious or not, which persist at the end of the study will be followed up by the Investigator until their resolution. Additional follow-up visits may be arranged to enable this. As appropriate, participants with ongoing AEs may be advised to consult their General Practitioner (National Health Service) or the study team will arrange specialist review within the NHS. The outcome of all related non-serious AEs and any SAEs will be assessed as:

Recovered/resolvedRecovered with sequelae/resolved with sequelaeUnknownOngoing at end of studyFatal

